### Participants and enrollment

We plan to recruit eligible subjects who meet the following inclusion criteria: (1) American Society of Anesthesiologists (ASA) class I-III, (2) adult subjects who are 18–75 years of age, and (3) subjects scheduled for elective video-assisted thoracoscopic single or multi-port lung surgery under general anesthesia with bronchial intubation.

The exclusion criteria are as follows: (1) trauma and emergency subjects, (2) subjects with New York Heart Function Scale (NYHA) levels of 3–4, (3) patients with heart conduction block (sinus block or atrioventricular block), (4) patients with unstable coronary artery disease, (5) patients with gastric ulcer or gastric bleeding, (6) patients with body mass index (BMI) of <18 kg/m^2^ or > 37 kg/m^2^, (7) patients with diabetes and are being treated with insulin, (8) patients with renal dysfunction (serum creatinine values exceed normal thresholds), (9) patients with liver dysfunction (Alanine aminotransferase or Aspartate aminotransferase is more than twice the normal value), (10) subjects with coagulation dysfunction (prothrombin time or activated partial thromboplastin time is higher than the normal threshold) or patients who are taking oral anticoagulants for other medical reasons and have not stopped it before surgery, such as warfarin or new anticoagulants rivaroxaban or dabigatran, (11) subjects with alcohol abuse or heavy dependence on narcotic drugs in the last 2 months, (12) subjects with uncontrolled anxiety, schizophrenia, or other mental illness, (13) subjects who are pregnant or preparing for pregnancy, and (14) subjects with a history of allergy to local anesthetic drugs or any of the experimental medications. Written informed consent will be signed by participants before enrollment.

### Randomization and blindness

A research coordinator who would not participate in the subsequent study conducted the online randomization with a 1:1 ratio and permuted block size of 4.^1^ According to the random sequence, subjects were randomly assigned to either the liposomal bupivacaine group (LB) or the bupivacaine HCl group (BUPI). The allocation concealment was guaranteed using identical opaque sealed envelopes. An independent anesthesia nurse at each study center prepared the study medications, either liposomal bupivacaine or bupivacaine HCl, according to the random results. As liposomal bupivacaine emulsions and bupivacaine HCl have different appearances, we ensure the blinding of surgeons and operating room staff by transferring the medication to an identical opaque syringe, which is labeled with the patient’s number only. The ESPB procedures will be performed by a skilled anesthesiologist at each center who will not be involved in managing anesthesia and overseeing postoperative care. All other perioperative clinical care will be carried out following institutional standard practice. All relevant data will be recorded on the trial case report form (CRF) and entered into the EDC system within 1 week of completing the CRF forms.

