**Methods:**

This multicenter, randomized, double-blind, controlled trial will include 272 adult patients scheduled for elective video-assisted thoracoscopic lung surgery. Patients will be randomly assigned, 1:1 and stratified by site, to the liposomal bupivacaine (LB) group or the bupivacaine (BUPI) HCl group. All patients will receive ultrasound-guided ESPB with either LB or bupivacaine HCl before surgery and patient-controlled intravenous analgesia (PCIA) as rescue analgesia after surgery. The numeric rating scale (NRS) score will be assessed after surgery. The primary outcome is the area under the curve of pain scores at rest for 0–72 h postoperatively. The secondary outcomes include the total amount of opioid rescue analgesics through 0–72 h postoperatively, time to the first press on the PCIA device as rescue analgesia, the area under the curve of pain scores on activity for 0–72 h postoperatively, NRS scores at rest and on activity at different time points during the 0–72 h postoperative period, Quality of Recovery 15 scores at 72 h after surgery, and NRS scores on activity on postsurgical day 14 and postsurgical 3 months. Adverse events after the surgery are followed up to the postsurgical day 7, including postoperative nausea and vomiting, fever, constipation, dizziness, headache, insomnia, itching, prolonged chest tube leakage, new-onset atrial fibrillation, severe ventricular arrhythmia, deep venous thrombosis, pulmonary embolism, pulmonary atelectasis, cardiac arrest, ileus, urinary retention, chylothorax, pneumothorax, and organ failure. Analyzes will be performed first according to the intention to treat principle and second with the per-protocol analysis.

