### Study design and status

This investigator-initiated, multicenter, randomized, double-blind, parallel-controlled trial will be conducted at 12 tertiary hospitals in China. Subjects will be randomized to receive either liposomal bupivacaine or bupivacaine HCl for ultrasound-guided ESPB after induction of anesthesia. Group allocation is performed by the online central randomization system.

This trial start date is 1 September 2023, and the anticipated end date is 31 March 2025. By the time of this manuscript submission, the recruitment of participants has started, but all follow-up data will be stored in the electronic data capture (EDC) system, which will be locked until the final analysis. Figure 1 shows the study flow diagram. Table 1 presents the schedule of subject enrollment, study intervention, and outcome evaluation following the SPIRIT statement.

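### A single fixed block size of 4 within site leaves about one allocation in three certain to anyone who knows that site's earlier allocations, and the article does not say how the online system and the sealed envelopes fit together

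*Protocol article*

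**What the plan says.** Under Randomization and blindness, a coordinator with no later part in the trial randomizes patients online "with a 1:1 ratio and permuted block size of 4". No other block size is mentioned. The Methods part of the abstract adds that assignment is "1:1 and stratified by site"; the randomization section does not repeat this. The trial "will be conducted at 12 tertiary hospitals in China" (Study design and status).

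Concealment is described in two places. Study design and status says: "Group allocation is performed by the online central randomization system". Randomization and blindness says: "The allocation concealment was guaranteed using identical opaque sealed envelopes". The article does not connect the two statements.

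On who knows the arm, the randomization section says: "An independent anesthesia nurse at each study center prepared the study medications". It acknowledges that the two drugs differ in appearance and relies on opaque syringes, marked only with a patient number, to blind the surgeons and operating room staff. The person who performs the block takes no part in anesthesia management or postoperative care. Table 1 places screening and consent on study days -6 to 0, and randomization and allocation 2 h before surgery.

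**The concern.** In permuted blocks of one known size, the end of each block can be worked out from its beginning. When blocks run within site, the site's own allocation history is all that is needed. The opaque syringe hides the arm from those who receive it but not from the preparer, so knowledge of the arm exists at every center.

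If that knowledge reached someone who decides whether or when a patient is entered, patients could be deferred, reordered or left out according to the coming drug. Consent can precede allocation by days in elective surgery, so some freedom over order remains. Blinding during surgery and follow-up does not repair selection that happens at entry.

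The two descriptions of concealment matter for the same reason. A central system that releases one result at a time protects the next allocation differently from an envelope held on site. As written, a reader cannot tell which of them did the protecting.

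**Working it through.** **Inputs.** Allocation 1:1 in blocks of 4 (Randomization and blindness); stratification by site (abstract); 12 hospitals (Study design and status); 272 patients (Sample size calculation).

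**The plan's own figure.** The article gives no predictability figure. Its total of 272 serves here only to turn a proportion into a count. With a difference of 15, SD 38.7, 80% power and two-sided 0.05, the t-test needs 106 per arm. Then 106/0.8 = 132.5, rounded up to 133, which makes 266 in total. That is within 3% of 272, so 272 is used as stated.

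**Certainty within a block of 4.** There are 6 equally likely orders of two LB and two BUPI. An allocation is certain once one arm is used up.

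| Position | Chance the allocation is certain | Chance the best guess is right |
|---|---|---|
| 1 | 0 | 1/2 |
| 2 | 0 | 2/3 |
| 3 | 1/3 | 2/3 |
| 4 | 1 | 1 |

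- Position 3 is certain when the first two allocations match, which happens in 2 of the 6 orders.
- Certain allocations: (0 + 0 + 1/3 + 1)/4 = 1/3.
- Best guess: (1/2 + 2/3 + 2/3 + 1)/4 = 2.833/4 = 70.8%, against 50% by chance.

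**Scaled to the trial.**
- All blocks complete: 272/3 = 90.7, about 91 patients.
- Incomplete last blocks, assuming 12 equal sites (8 with 23 patients and 4 with 22). Five complete blocks give 5 × 4/3 = 6.67 certain allocations. A site of 23 adds 0 + 0 + 1/3, giving 7.00; a site of 22 adds 0, giving 6.67. The total is 8 × 7.00 + 4 × 6.67 = 82.7, about 83 patients, or 82.7/272 = 30.4%.

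**Alternatives.** Fixed sizes of 6 and 8 were enumerated in the same way. Mixed sizes were simulated with 24 patients per site, each block size equally likely. The observer knows which sizes are possible but not the order in which they occur.

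| Scheme within site | Certain | Best guess right | Largest possible imbalance |
|---|---|---|---|
| Fixed 4 | 33.3% | 70.8% | 2 |
| Fixed 6 | 25.0% | 68.3% | 3 |
| Fixed 8 | 20.0% | 66.6% | 4 |
| Random 4 and 6 | about 5.9% | about 68.7% | 3 |
| Random 4, 6 and 8 | about 2.3% | about 67.2% | 4 |

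The largest imbalance is half the largest block. Varying the size removes most of the certainty but little of the general guessability.

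**The case against.** The strongest reply is that predictability does harm only if someone who controls entry knows the earlier allocations, and the article supplies no such link. It names an outside coordinator, an independent nurse, syringes identified only by number, and a block operator kept apart from other care. Allocation comes 2 h before surgery, after consent. A recruiter would therefore need both the site's history and the patient's eventual place in the block. This stands, and it limits the point to a vulnerability. It does not make a fixed block of 4 less predictable, and reordering on the day of surgery remains possible.

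The two concealment statements may also be compatible: the coordinator could obtain each result online and pass it to the nurse in a sealed envelope. That is a fair reading, but the article does not say so. A reader might infer that envelopes for future patients were stocked at the sites; this is not stated either.

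Two other inferences are tempting. One is that the nurse works alongside those who recruit, or sees every allocation at the site in order. The article says only that the nurse is independent and prepares the drugs. The other is that publication exposed the block size while recruitment was open. The article says that recruitment had started at manuscript submission, shows no publication date, and expects the trial to end on 31 March 2025, with a 3-month outcome still to be collected after the last operation. How many patients remained is unknown.

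**Conclusion.** The point holds as a weakness of design and description. Given a site's earlier allocations, one third of allocations in complete blocks are certain (about 91 of 272), or about 30% (about 83) with 12 equal sites and incomplete last blocks. The best guess succeeds 71% of the time.

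This rests on blocks running within site, which only the abstract states. If blocks of 4 ran across all sites, one site's history would not give this certainty. The certainty comes from the fixed size. The nurse's knowledge and the unclear envelope step bear only on who could use it.

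A reader might go on to infer selection bias, or a shift of some size in the pain AUC difference. The documents do not support either. They give no sign that anyone acted on foreknowledge, and no basis for the share of patients who might be steered or how far their pain scores would differ. No bias estimate is offered.

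**What to change.** 1. For any patients still to be randomized, have the central system use randomly varying block sizes within site, for example 4 and 6, or 4, 6 and 8, without disclosing the sizes to the sites. Certain allocations fall from 33% to about 6% or 2%.
2. Release each allocation only after the patient has been irrevocably entered. Allocation 2 h before surgery, after consent, already goes part of the way.
3. Reconcile Study design and status with Randomization and blindness. State how the online central system and the sealed envelopes fit together, and which of them conceals the next allocation. The sponsor must say what was actually done; the text does not show which description is right. This is needed even if recruitment has ended.
4. Repeat in the randomization section that blocks run within site, if they do.

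The cost is a setting in the randomization system and a wording change. The largest possible imbalance between arms within a site rises from 2 to 3 (sizes 4 and 6) or 4 (sizes 4, 6 and 8). The gain is mainly in certainty: the best-guess rate falls only from about 71% to about 67–69%, so keeping earlier allocations from those who enroll patients remains necessary.

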### Study interventions

The drugs are prepared as follows: liposomal bupivacaine (20 mL, 266 mg) is diluted to 30 mL with 10 mL of normal saline in the LB group, while bupivacaine HCl (100 mg) is diluted to 30 mL with 10 mL of normal saline in the BUPI group. After the induction of anesthesia, an independently trained anesthesiologist performs single-injection ESPB under ultrasound guidance in the lateral position. Initially, a high-frequency linear ultrasound probe is used in a vectorial position to locate the T4 spinous process longitudinally, and then the probe is moved outward to target the T5 transverse process. Guided by planar ultrasound visualization, the nerve block operator carefully advances the needle until the top reaches the T5 transverse process bone, and then 30 mL of local anesthetic is injected slowly after the confirmation of no blood or cerebrospinal fluid with a syringe aspiration.

All subjects will receive patient-controlled intravenous analgesia (PCIA) as rescue analgesia after surgery using 100 μg of sufentanil diluted to 100 mL with normal saline (a final concentration of 1 μg/mL). The parameters for the PCIA device are as follows: no background infusion, a self-controlled bolus of 2 mL, a lockout time of 5 min, and a locking dose of 20 mL per hour. PCIA is started once the patients enter the recovery room. Patients are instructed to self-administer sufentanil using PCIA to treat pain on the numeric rating scale (NRS) score of ≥4. If the pain remains unrelieved, additional rescue medications with morphine of 2–5 mg or other opioid analgesics can be slowly injected intravenously. The PCIA is discontinued after 48 h postoperatively. Later, if subjects still experience pain (NRS scores ≥4), morphine of 5–10 mg or other opioid analgesics can be administered. Subjects in both groups receive oral celecoxib of 200 mg twice daily (at 08:00 and 16:00) as a component of the multimodal analgesic regimen from the first postsurgical day (day 2) until complete pain relief. Oral celecoxib can be used after hospital discharge if necessary.

### Perioperative management

The flow of the participants through this trial is depicted in Figure 1. Subjects do not receive sedative or analgesic medications preoperatively. In the operating room, standard monitoring includes electrocardiography, non-invasive cuff blood pressure, pulse oximetry, and temperature. The left or right radial artery is cannulated following anesthesia induction, and continuous radial artery pressure is measured. General anesthesia is induced with propofol (2–2.5 mg/kg), sufentanil (0.3–0.5 μg/kg), and cisatracurium (0.2 mg/kg) in sequence. Following tracheal intubation with a double-lumen tube, unilateral bronchial ventilation is conducted with a tidal volume of 4–6 mL/kg and a respiratory rate of 12–16 times/min, aiming to maintain the end-tidal carbon dioxide at 35–45 mmHg and pulse oxygen saturation of ≥95%. The location of the bronchial tube is then confirmed using flexible fiberoptic bronchoscopy. Anesthesia is maintained with sevoflurane inhalation targeting a bispectral index value between 40 and 60. Intraoperative analgesia is provided with sufentanil and remifentanil: sufentanil 0.1–0.2 μg/kg is given before incision at the beginning of surgery, and remifentanil (0.05–0.2 μg/kg/min) is infused continuously for intra-operative analgesia. Additional doses of sufentanil can be given intraoperatively if necessary, and sufentanil is added 0.1–0.2 μg/kg when the remifentanil is discontinued at the end of the operation. The additional doses of cisatracurium can be incremented intraoperatively as needed. Intraoperative hypotension (defined as a decrease in mean blood pressure [MBP] of >20% of baseline or MBP of <65 mmHg) would be treated with intravenous ephedrine of 6–10 mg or phenylephrine of 50–100 μg, and bradycardia (defined as heart rate [HR] of <50 beats/min) would be treated with intravenous atropine of 0.3–0.5 mg.

At the end of the surgery, all subjects received ondansetron of 8 mg as an antiemetic after the last stitches. Subjects are transferred to a post-anesthesia care unit (PACU) and kept there for at least 1 h before returning to the thoracic ward. The surgical day is regarded as the study day 1, and the day following surgical day is the study day 2.

### Postsurgical assessments

Pain intensity assessments are conducted at 0 h (~15 min after extubation), 1 h (± 10 min), 6 h (± 2 h), 12 h (± 2 h), 18 h (± 2 h), 24 h (± 2 h), 32 h (± 2 h), 40 h (± 2 h), 48 h (± 2 h), 60 h (± 2 h), and 72 h (± 2 h) postoperatively, and at patient’s request for rescue medication, where the time of the completion of surgery is considered 0 of the postoperative time. Pain intensity is assessed using an 11-point NRS (0 = no pain; 10 = worst possible pain) at rest and on activity; the latter refers to the scoring when turning over on bed if the subjects are still not out of bed for activity, or the scoring on active movement if the subjects are already out of bed. Telephone follow-up is performed if the subjects are discharged from the hospital within 72 h. During the nighttime (23:00 to 06:00, the next day), the subject is not awakened for scoring. If the subject is awake during the time window, the NRS score is assessed based on the subject’s own or companion’s recollection in the following morning; if the patient is asleep during the time window, the NRS score is standardized to a uniform value of 2. Considering the potential impact of opioid rescue medications on pain measurements, the windowed worst observation carried forward (wWOCF) method is utilized to accurately document NRS pain scores in the initial 72 h following surgery. The wWOCF approach operates in the following manner: to obtain the wWOCF for subjects who receive rescue medication, any NRS scores noted within a 2-h “window” following the administration of opioid rescue medication are replaced by the highest (“worst”) NRS scores recorded before the administration of their initial rescue medication. The time to the first rescue analgesia using PCIA was recorded, and the amount of medication used for rescue analgesia with the PCIA analgesic pump was also calculated. Quality of Recovery 15 (QoR-15) scores at 72 h after surgery are used to evaluate the subject’s recovery. NRS scores are measured once daily after 72 h postoperatively until study day 15. The number of continued days and the dosage of the oral analgesic drug celecoxib after discharge are also recorded.

### Data monitoring committee

An independent Data Monitoring Committee (DMC) comprising experienced anesthesiologists and statisticians has been established to resolve any uncertainties related to data collection and to determine whether postsurgical analgesic medications that have been administered are beyond the protocol. This DMC comprises a chair (an experienced anesthesiologist), an attending anesthesiologist, two statisticians, and an attending thoracic surgeon. When ambiguity occurs in data collection or in adherence to protocol medications, these issues are discussed at the DMC to reach a final conclusion.

### Trial outcome definitions

#### Primary outcome

The primary outcome for the trial is the area under the curve of pain scores at rest for 0–72 h (AUC NRS-R_0-72_) postoperatively.

#### Secondary outcomes

The secondary outcomes include (1) the total amount of opioid rescue analgesics through 0–72 h postoperatively, (2) the time to first press on the PCIA device as rescue analgesia, (3) the area under the curve of pain scores on activity for 0–72 h (AUC NRS-A_0-72_) postoperatively, (4) NRS scores at rest and on the activity at different time points during the 0–72 h postoperative period, (5) Quality of Recovery 15 (QoR-15) scores at 72 h after surgery, (6) NRS scores on activity on postsurgical day 14 (study day 15), which will be followed up via telephone, with a permitted time window of 14 ± 3 days, and (7) NRS scores on the activity at postsurgical 3 months will be followed up via telephone, with a permitted time window of 3 months ±7 days. Opioids are first converted to intravenous morphine equivalents for each subject, and then the total amount will be naturally logarithmically converted before analysis. The time to first opioid rescue analgesia using PCIA was measured in hours, i.e., the date and time of the first opioid rescue minus the date and time of the end of surgery.

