### Sample size calculation

Between January 2023 and March 2023, we conducted a prospective study on two groups of 10 patients each. All participants underwent video-assisted thoracoscopic lung surgery and were administered a preoperative ultrasound-guided ESPB, with one group receiving liposome bupivacaine and the other bupivacaine HCl. The results showed that the postoperative AUC NRS-R0-72 was 247 ± 35 in the LB group versus 262 ± 43 in the BUPI group. Based on the preliminary study, the sample size was determined to ensure the ability to detect a mean difference of 15 in the primary efficacy outcome, and we suggest that this difference is clinically relevant. This calculation is performed with a two-group *t*-test, a standard deviation of 38.7, an 80% power, and a 0.05 level of significance. Considering a 20% dropout rate, this study will enroll a total of 272 patients, with 136 in each group. The sample size is calculated using the SAS software (version 9.4, SAS Institute Inc).

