Demographic information and baseline characteristics will be described using descriptive statistics only, with no between-group comparisons. Continuous data will be displayed as means and standard deviations or medians and interquartile ranges, depending on data distribution. Categorical data will be summarized as counts and percentages. Between-group differences of continuous data will be analyzed using the independent t-test or Mann–Whitney rank sum test as appropriate, while categorical data will be analyzed using the Chi-squared test or Fisher’s exact test as appropriate. To analyze the treatment effect, odds ratios are calculated for binary data and mean differences for continuous data, each together with their 95% confidence intervals. For the primary outcomes, the between-group difference of AUC NRS-R_0-72_ is regarded as significant at the two-side *p*-value of 0.05. For the secondary and tertiary outcomes, multiple comparisons are adjusted for the significance level of probability values by computing the false discovery rate using the Benjamini-Hochberg method. To further understand the cumulative effect of study interventions on postsurgical pain, *post-hoc* analysis is conducted, including AUC NRS-R_0-24_, AUC NRS-R_24-48_, AUC NRS-R_48-72_, AUC NRS-A_0-24_, AUC NRS-A_24-48_, and AUC NRS-A_48-72_, the cumulative amount of opioid rescue analgesics during 0–24, 24–48, and 48––72 h, and the proportion of subjects who are pain-free (NRS-R score of 0 or 1) at 1, 6, 24, 48, and 72 h. To address the missing NRS pain intensity scores during the postoperative 0–72 h, interpolation is performed using one of the following methods: (1) by last observation carried forward (LOCF) imputation method if missing data are located after the last non-missing score, (2) by linear interpolation if more than one missing data occur and are located between two non-missing scores (25). All data will be analyzed using the SAS software (version 9.4, SAS Institute Inc) by an independent statistician.

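### The log rule for total rescue opioid is undefined for patients who use none; applied as written, it would lose them from the first secondary outcome

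*Protocol article*

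**What the plan says.** The Secondary outcomes section lists first "the total amount of opioid rescue analgesics through 0–72 h postoperatively". Opioids are converted to intravenous morphine equivalents for each patient, and then "the total amount will be naturally logarithmically converted before analysis". The rule is unconditional.

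The Study interventions section sets the pump to "no background infusion, a self-controlled bolus of 2 mL". On use it says: "Patients are instructed to self-administer sufentanil using PCIA to treat pain on the numeric rating scale (NRS) score of ≥4". Further opioid is given only if pain is not relieved, or if it persists after the pump is stopped at 48 h.

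The Statistical analysis section offers a choice of tests: "Between-group differences of continuous data will be analyzed using the independent t-test or Mann–Whitney rank sum test as appropriate". It defines the intention-to-treat population as randomised patients who had the block, completed surgery and have a primary outcome; use of rescue opioid is not a condition. Its missing-data rules concern pain scores only.

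**The concern.** A total of zero is a real and favourable value of this outcome, yet the stated transformation has no result for it. In most software the log of zero becomes missing or minus infinity, and the patient then leaves the comparison or the mean cannot be computed.

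If zero users are lost, the analysis compares users with users. Whether a patient needs any rescue opioid is itself affected by the block, so the groups compared are no longer those formed by randomisation. A longer-acting block could plausibly show part of its benefit as more patients who need no opioid at all, and a users-only analysis cannot see that part.

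**Working it through.** **1. Can the total be zero?** Yes. There is no background infusion, each bolus is patient-initiated, and other opioids are given only for persisting pain. The Postsurgical assessments section also does not treat rescue as universal: its score-replacement rule is worded "to obtain the wWOCF for subjects who receive rescue medication".

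**2. Is zero plausible?** The Sample size calculation section reports that "the postoperative AUC NRS-R0-72 was 247 ± 35 in the LB group versus 262 ± 43 in the BUPI group". Divided by 72 h:
- LB: 247/72 = 3.43, SD 35/72 = 0.49
- BUPI: 262/72 = 3.64, SD 43/72 = 0.60

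Both time-averaged rest scores lie below the rescue threshold of 4, so zero use is plausible. This does not give a rate, because averages hide peaks and the threshold is not limited to rest pain.

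**3. What does the rule give?** ln(0) is undefined (numerically minus infinity). The log is taken before the analysis, so neither listed test recovers a patient whose value has become missing.

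**4. How many patients?** The documents do not say. Assumed zero shares applied to 136 per arm:

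| Zeros LB / BUPI (assumed) | Lost LB | Lost BUPI |
|---|---|---|
| 5% / 2% | 136 × 0.05 ≈ 7 | 136 × 0.02 ≈ 3 |
| 10% / 5% | ≈ 14 | ≈ 7 |
| 20% / 10% | ≈ 27 | ≈ 14 |
| 30% / 15% | ≈ 41 | ≈ 20 |

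**5. What does it do to the comparison?** Simulation with 109 evaluable per arm (136 × 0.8 = 108.8), lognormal doses among users with SD 0.8 on the log scale, and 2,000 to 3,000 trials per row. Every input except the arm size is an assumption. Entries are the share of trials with p < 0.05, without the false-discovery adjustment.

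| Zeros LB / BUPI | Users' doses, LB vs BUPI | Log t-test, zeros dropped | Mann–Whitney, all patients |
|---|---|---|---|
| 10% / 5% | equal | 5% | 10% |
| 20% / 10% | equal | 5% | 25% |
| 20% / 5% | equal | 5% | 47% |
| 30% / 10% | equal | 5% | 73% |
| 2% / 1% | 25% lower | 76% | 74% |
| 5% / 2% | 25% lower | 74% | 80% |
| 10% / 5% | 25% lower | 72% | 82% |
| 20% / 5% | 25% lower | 70% | 98% |

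With equal doses among users, the whole effect lies in the zeros. At 20% / 5%, for example, the true ratio of means is 0.80/0.95 = 0.84, but the users-only analysis rejects only at its type I error rate. With an effect among users as well, the loss is nil when zeros are rare and grows with the difference in zero shares.

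**6. Does the choice of remedy matter?** Yes. At 20% / 10% zeros and equal doses among users, with a user median of 10 mg, rejection is 25% with Mann–Whitney, 38% with ln(x+1), 47% with ln(x+0.1) and 50% with ln(x+0.01). A choice made after unblinding would be a real degree of freedom.

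**7. Primary outcome.** The sample size rests on the rest-pain area under the curve. A difference of 15, SD 38.7, two-sided 0.05 and 80% power give 106 per arm by the t-test. Then 106/0.8 = 132.5, so 133 per arm and 266 in total, close to the stated 272. Nothing here depends on the opioid outcome.

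**The case against.** **No text excludes zero users.** A reader might infer that the plan drops the patients with the best analgesia. It does not say so: the intention-to-treat definition would keep them, and the full protocol or analysis plan, not shown, may hold an offset. This stands, so the loss is conditional on literal application and on at least one patient with zero use. But the point is more than silence on a detail. The article commits to a transformation that cannot be computed over part of the outcome's range, and literal application conflicts with its own population.

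**A rank test is already listed.** This is true, and a reader should not infer that the plan has no rank method. If zeros were kept as the lowest values, the log would leave the ranks unchanged. The difficulty is only that the log comes first and may remove the zeros.

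**The zero rates are guesses.** This stands. A zero total needs 72 h without a press or any other opioid, and movement pain can also trigger rescue. Two SDs below the pilot LB mean is still a rest score of about 2.5 (3.43 − 2 × 0.49). The pilot leaves zero use possible but does not support 20–30%. The equal-dose rows are also the least favourable case for a users-only analysis, so a general claim of no power is not supported.

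**Interval totals.** A reader might extend the point to "the cumulative amount of opioid rescue analgesics during" the three 24-hour periods, above all 48–72 h, after the pump is stopped. The log rule is stated for the secondary-outcome total, and these period analyses are listed as post hoc without a log, so the text does not support that extension.

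**Conclusion.** The point holds in conditional form. The rule for the first secondary outcome has no result for a legitimate value. Applied as written, zero users would be lost, contrary to the defined population, and the comparison would miss any benefit that appears as more opioid-free patients.

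The size cannot be derived from the documents. On the assumptions above, it runs from about nil at 1–2% zeros to a large loss of power at 20–30% zeros in the LB arm, and it depends on how the effect is split between the share of zero users and the dose among users. The affected result is one of seven secondary outcomes under false-discovery adjustment. This is a should-fix, not a flaw that threatens the trial's main conclusion.

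**What to change.** Before unblinding, replace the log sentence with a rule that covers zeros:
- Analyse all patients, zeros included, on untransformed intravenous morphine equivalents with the rank test already listed. A site-stratified form (van Elteren) is preferable, since the Abstract says randomisation is stratified by site.
- Report a Hodges-Lehmann difference with its 95% confidence interval, and the proportion with zero use per arm.
- If a log model is kept, use ln(x + c) with c and the unit fixed in advance, as a sensitivity analysis.

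The cost is a sentence or two of text and no new data. The drawback is that the geometric-mean ratio is no longer the main estimate. The rank test is also not the most powerful choice in every scenario: at 20% / 10% zeros with equal doses among users it rejected in 25% of trials, against 38% for ln(x+1). Its advantage is that the result does not depend on an arbitrary constant.
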